**Figure 2 Flow diagram for direct mail-out of self-sampling kits**

[figure not shown]

### 7.2.2 Opportunistic offering

Women targeted for opportunistic offering will be identified using the GP patient record software system (date of last recorded cervical screening test). Although cervical screening records in GP records are sometimes not up to date, this method of identifying the relevant cohort for opportunistic offering is currently the only viable option (GP patient records are not linked to the national screening database (NHAIS)).

An alert will be set up on the electronic patient record (EPR) software to automatically flag potentially eligible women when their record is opened. Specifically, EPR systems will be programmed to flag women aged 25.5-64 years who are at least 6 months overdue cervical screening (i.e. no cervical screening test (cytology, HPV primary or self-sample) recorded in the past 3.5 years (if aged 25-49) or 5.5 years (if aged 50-64) and no codes for hysterectomy or amputation of cervix). The alert will be switched on at the practice start date.

Doctors, nurses and healthcare assistants (HCA)/assistant practitioners (AP) will be asked to offer self-sampling kits to women who have been flagged when they consult for any reason. In practice, this will be on a case-by-case basis at the discretion of the healthcare professional consulted. The trial invitation (kit offer) will comprise a brief conversation (~2 minutes) at the end of the consultation. Healthcare professionals will be asked to confirm the women's eligibility before handing them a self-sampling kit, which includes the patient information booklet.

A study template will be set up in the GP electronic patient record system. When women are offered kits, the consulting health professional will use the template to record:

- 1) Whether or not the trial kit was accepted.

- 2) If accepted: trial kit ID number
- 3) If declined:
  - a) Reason for declining (if logistics allow)
  - b) Consent or dissent to share anonymous data from their GP records and the national cervical screening database

If the woman accepts a kit, the consulting health professional will:

- Print out a lab request/consent form with the woman's details mail-merged using the EPR system to be returned with the sample
- Write the kit ID number on the lab request/consent form
- Write three of the NHS CSP acceptable identifiers on the tube label. Preferably these will comprise the woman's name, date of birth and postcode.

To ensure optimal uptake women will be encouraged to collect the sample at the GP practice, but will also have the option of taking their kit away to collect the self-sample at home.

Depending on where the sample is collected, either the healthcare professional (clinic) or the woman (home) will write the date the sample was taken on the tube label and the lab request/consent form. Healthcare professionals will be asked to only enter a sample date on the tube label and lab request/consent form once women have collected a sample, to avoid the incorrect date appearing if women take the kit home and sample at a later date.

If possible, self-samples that are collected at the GP practice will be collected by the usual central laboratory collection services and delivered to the laboratory. If this is not possible, samples will be posted to the laboratory daily by the GP practice administrative staff using freepost, pre-addressed envelopes.

Women who collect their self-sample at home will post it directly to the laboratory (Royal Mail freepost in line with Packaging Instruction P650 for biological substances classified as UN3373) for analysis.

Opportunistically offered kits will comprise:

- A CE-marked dry flocked swab (552C.80 Copan FLOQswab™) in a tube with a re-sealable lid
- Pictorial and written instructions for self-collecting the vaginal sample
- A UN3373-compliant freepost envelope (padded or polybag) or box that is pre-addressed to the laboratory
- A patient information booklet
- A specimen bag
- A questionnaire (questionnaire-based sub-study)

Once a valid self-sample result (i.e. either Human papillomavirus self-sample test positive or Human papillomavirus self-sample test negative. Results for unavailable/Insufficient self-sample for human papillomavirus testing will be ignored) has been coded into the electronic GP records the alert will be programmed to switch off. With this trial design, potentially women may receive more than one kit offer, either opportunistically if they consult more than once during the trial period or if they are sent a kit via direct mail-out and are offered self-sampling opportunistically at their GP practice prior to an adequate self-sample result being entered. The rationale for allowing women to be offered kits opportunistically more than once is because in our previous study we found that women who declined kits accepted subsequent offers. This could happen for example if women are feeling particularly unwell at the first offer and in better health at the subsequent visit.

The laboratory will have a protocol to ensure that it rejects self-samples if one has already been tested in that screening round (i.e. in the last 3 years if aged 25-49 or the last 5 years if aged 50-64) unless the self-sample recorded was not reportable because it was unavailable or not returned in the acceptable time frame for sample validity.

**Figure 3 Flow diagram for opportunistic offering of self-sampling**

[figure not shown]

### 7.2.3 Optimising self-sampling uptake

We will use various approaches to help optimise self-sampling uptake. These include:

- A communication campaign will be developed by Claremont Communications to enhance the uptake of the kits. Claremont will deliver a targeted communications campaign to aid the recruitment and maximise uptake of self-sampling in our target population (women aged 25-64 in the boroughs of Camden, Barnet, Tower Hamlets, Islington and Newham who are at least 6 months overdue their smear test). The communications campaign will target audience's influencers, e.g. family, friends, healthcare professionals (GPs, pharmacists and practice nurses), charities, community groups, religious groups and other influencers. Claremont's campaign package will include the development of posters and leaflets. The focus of the messages will be to raise awareness and highlight that invited women will receive a kit (postal approach) or be provided one at their GP practice (opportunistic). The posters will be distributed to several stakeholders for display in key places such as GP practices, community pharmacies, sexual health clinics, community and faith organisations and offices of large employers such as local councils. Information about the trial will also be featured in local media in the respective CCGs, council and community organisation newsletters. Key organisations such as the CCGs, councils and community organisations will also be provided information to feature on their websites and social media channels. This content will also be featured on the UCLH and Small c websites (as detailed further below). The campaign package will also include a video raising awareness of the trial. The video will be featured on websites of the stakeholders that disseminate the other campaign materials as well as the UCLH and Small C websites.
- A web page with information about the trial will be hosted by the North Central and East London Cancer Alliance Small c website <https://www.smallc.org.uk/>. The Small c website has the "Recite me" functionality which allows the website to be fully accessible. Visitors to the site can customise the site the way they need it to work for them. The website has a translation tool for over 100 languages and text to speech functionality for 30 languages.
- The small C website will also include an animated video for women with instructions on how to take a sample.

- To educate GPs, a training video about the trial will be made available on the North Central and East London Cancer Alliance website, shared directly with practices and if possible, linked to from the YouScreen EMIS template.
- A self-sampling telephone helpline will be run by Jo's cervical cancer trust <https://www.jostrust.org.uk/> for women offered kits to address any questions they have on the trial or how to take the self-sample. The helpline will provide clear, reliable and trustworthy information around self-sampling, HPV, HPV testing, cervical screening, symptoms, colposcopy, treatment for cell changes and cervical cancer.
- If uptake is lower than expected, we may send a reminder postcard or letter to women who have received kits (via either mode of kit offer) but not returned kits within 4 weeks.(32) A substantial amendment will be submitted for this.

## **7.3 Consent**

The YouScreen patient information booklet, pre-notification letter and invitation letters will be translated into the top 3-5 most commonly requested languages in North Central & East London (Turkish, Bengali, Polish, Arabic, Somali) and made available on the small C website. As mentioned previously, the Small c website has the “recite me” translation tool for over 100 languages and text to speech functionality for 30 languages.

As this is a pragmatic implementation feasibility trial that will closely mimic the NHS CSP screening pathway in order to ensure optimal uptake in a hard to reach population, this study will not include a signed consent form.

### **7.3.1 Consent at GP practice level**

Firstly, consent will occur at the GP practice level. Each GP practice will provide consent confirmation (via the Organisational Information Document) for their practice to take part and for eligible women to be sent kits for the trial. GP practices will consent to aggregate anonymised patient data being collated from their Electronic Patient Record systems (EMIS web) for monthly study reporting, and de-personalised line-level data on all eligible women including women who do not return a self-sample). We will seek CAG approval for this, particularly as this data will be downloaded centrally at the CCG level.

### **7.3.2 Consent at individual women level**

This trial will be conducted as closely as possible to the likely pathway self-sampling at the national level. The patient information booklet (including information on HPV) will be provided to all women who receive self-sampling kits. As only women who wish to participate will return a self-sample (i.e. opt-in), consent is implicit.

The lab request/consent form and invitation letter will clearly state that if the women choose to complete the self-sample and send the kit to the laboratory that they are consenting to participate in the trial. The patient information booklet will specify the relevant details about the laboratory testing, retention of residual samples for future research, access to their data, and passive follow up data including line individual level linkage to previous and future cervical screening outcomes for women who consent to residual sample retention. It will also be clearly stated that this test will be completed instead of the cervical screening test taken by a doctor or nurse. The women will be informed that if they prefer to book a cervical screening appointment with a doctor or nurse that they are free to do so.

The lab request/consent form will comprise of an initials box to allow participants to opt in for their residual samples to be stored with their personal details removed for future ethically approved research.

### **7.3.3 Opportunistic offering of self-sampling**

GP primary care is a busy and time-pressured environment with an average GP consultation length of just 9 minutes.(33) In a previous study of opportunistic offering of self-sampling in GP primary care the consent procedure consisted of a brief (2 min) study explanation and verbal consent. This simplified approach was suggested by the reviewing REC committee (Brighton and Sussex NRES Committee 13/LO/1441 and 17/LO/1655) and worked well for the study with no issues raised. Therefore, we intend to use the same verbal consent procedure for this trial. Consent to accept a

self-sampling kit will be recorded in the women's GP medical record, regardless of whether or not they return a self-sample. The lab request/consent form will not be signed.

### **7.3.4 Women sent kits via direct mail-out**

Consent will be implicit by return of a self-sample.

Self-Sample Kits (SSKs) will come with a lab request/consent form which will contain the women's details (to identify the women) and statements detailing what the trial involves and what they are agreeing to by returning a self-sample (e.g. regarding permission for the trial team to access to medical record data). The form will state clearly what the women are consenting to by returning their sample. The lab request/consent form will not be signed.

### **7.3.5 Opt-out procedures for women who do not consent to the trial**

YouScreen plans to collect anonymous line-level and aggregate data from NHAIS (the national screening database) and GP medical records (via the CCG) for women who do not consent to the trial. A Confidentiality Advisory Group (CAG) approval will be obtained for this activity (see 14.2 Confidentiality Advisory Group (CAG) approval).

We will provide any woman, who does not consent to the trial by returning the sample, and does not wish for her data to be used for the purposes of the trial, the opportunity to opt out of line level data collection.

The opportunities for opt-outing of data collection will include:

- Mailout offer: The invitation letter and patient information booklet sent to women who are identified as eligible for the mailout of kit will contain text advising women of the process for opting out of data collection.
- Fair processing notices in GP practices – these will be put up in all participating GP practices and will advise women to visit or call their GP Practice if they wish to opt out.
- Online - The Cancer Prevention Group webpage on the King's College website <https://www.kcl.ac.uk/lsm/research/divisions/cancer/research/groups/canprev/cancer-prevention-group> and the trial webpage on the Small c website <https://www.smallc.org.uk/> will contain details on data processing and sharing for YouScreen and will advise women to visit or call their GP Practice if they wish to opt out.

As opting out will require exclusion of women's data from two separate data sources; GP records and the national screening database (NHAIS), two steps will be executed by the GP Practice to ensure that the request for the opt-out is upheld. CSAS and NHS Digital will facilitate this process. KCL will not receive any patient identifiable data.

- The GP Practice staff will ask the woman for her details in order to code the woman's dissent into the electronic patient record.
- The GP Practice will then provide details of every woman who has opted out (full name, date of birth, NHS number and GP practice) to a trial specific email address managed by CSAS.
- CSAS will then take responsibility of providing a regular list to NHS Digital (via a secure support ticket system) of the women who have opted out.
- NHS Digital will verify the women's identify and then add her NHS Number to an 'exclusion list'.

The coding of the dissent into the electronic patient record will allow YouScreen study EMIS searches to be programmed to exclude data with this code in trial reporting datasets (apart from aggregate reports which do not require permission).

The exclusion list managed by NHS Digital will be applied to all NHAIS machines to ensure that the NHS number of any woman on this list is removed from the YouScreen NHAIS searches to identify women at the 15m anniversary for mailout and from the trial reporting datasets (apart from aggregate reports).

GP Practices will be provided with instructions for managing the opt-out process for the study at the Site Initiation Visit.

## 7.4 HPV testing, reporting and recording of results

Self-samples will be analysed for the presence of high-risk HPV DNA. Full details of the testing procedures are provided in section 7.6.

As this trial aims to test the new IT pathways for self-sampling, we plan to integrate self-sampling ordering, processing of samples, results recording and reporting as much as possible into the existing systems for cervical screening programme. Self-samples will be booked into the same laboratory information management system (LIMS) that the central laboratory service use for processing cervical screening under the NHSCSP. When cervical screening tests are taken at GP practices with electronic lab links set up, the sample is automatically booked into the central laboratory (LIMS), meaning that the laboratory already has the woman's personal and test details in their system before it arrives for analysis. No pre-booking of samples will be possible for kits directly mailed out because the screening programme and GP practice databases are not linked.

"Source of sample" is a compulsory field that needs to be inputted for all cervical screening tests under the Programme. To allow us to calculate uptake according to mode of kit offer, the laboratory will enter:

- 1 - "GP" for self-samples returned using opportunistically offered kits, and
- 6 - "Other" for self-samples returned via direct mail-out kits.

A specific range of kit ID numbers and potentially different coloured sample tube labels will be set up to assist the laboratory with distinguishing between the two kit types returned.

Results will be reported using the usual routes used by the NHSCSP:

- For sending results from the laboratory to GP practice: electronic lab links will be used (including automatic coding into EMIS Web) if available, otherwise results letters will be posted to the GP practice.
- For sending results from the laboratory to NHAIS: The central laboratory LIMS database and middleware (Keystone) software will automatically pick up self-sample test results and send the relevant list of results to NHAIS via Open-Exeter. Patient data are verified via Open-Exeter ensuring that the correct result goes to the correct woman. Self-sample results that are verified by Open-Exeter will then be dropped into the NHAIS database.
- For sending results to women: NHAIS will send the relevant results letter to the women (programmed into NHAIS for the trial).

The laboratory will aim to report HPV results (i.e. authorised report released to NHAIS) within 5 days of receiving a self-sample. Once an authorised report has been successfully released into NHAIS, the relevant results letter will be triggered for release within the NHAIS system (further details below in the following section). Women should receive their results letter within two weeks of returning a self-sample (as per current NHSCSP guidelines).

## 7.5 Clinical management & NHAIS (call/recall) pathway

NHS Digital will implement the changes required in NHAIS to support self-sampling. A specification outlining the changes required in the system to support the self-sampling pathway has been jointly drafted with input from NHS Digital, the trial team, clinical experts (consultant gynaecologist and GPs on the Joint Steering Group), PHE, Research Advisory Committee (RAC) and HSL laboratory. This includes appropriate failsafe measures for cervical screening self-sampling. **4Error! Reference source not found.** summarises the clinical management for women who return a self-sample in the trial and the associated self-sampling pathway in the national cervical screening database NHAIS (call/recall). Self-sampling will be recorded in NHAIS and will elicit the relevant changes in the call/recall pathway in NHAIS. This will allow us to accurately calculate the impact of self-sampling on coverage and to test the IT pathways. Proposed NHAIS codes for self-sampling are in Table 1.

### 7.5.1 HPV Negative

Women who test HPV negative on a self-sample will not require any further action or tests. They will have their NTDD reset within the national cervical screening (call/recall) programme according to age (3 years if aged 25-49y, 5y if aged 50-59, or if aged 60 or above at the time of testing, they will be ceased from the cervical screening programme (in keeping with the usual auto-ceasing rules).

### **7.5.2 HPV Positive**

Women who test HPV positive on a self-sample will be advised in their results letter to have a clinician sample – a conventional cervical screening test (HPV primary test triaged with reflex cytology if HPV positive) taken by a doctor or nurse at their GP practice. These women who subsequently undergo a conventional cervical screening test will be managed according to their HPV primary screening results as per routine clinical care under the NHS CSP.

The call/recall status for women who test HPV positive on a self-sample will be updated in NHAIS to early recall in 3 months, and her NTDD will be set to 3 months from the date the self-sample was taken (as recorded on the sample tube and lab request/consent form). As cells from the cervix are not exfoliated for self-sample collection, the follow up test (conventional cervical screening test) can be taken immediately (i.e. does not require the stipulated 3 month period in between conventional cervical screening tests to allow cells to regenerate). Therefore, NHAIS will be programmed to ensure it will accept any conventional cervical screening test immediately following an HPV positive on a self-sample result.

If a follow up test (conventional cervical screening test) is not received in NHAIS within 10 weeks of the reset NTD (3m), the woman will be added to her GP practices' Prior Notification List (PNL). The PNL is a list of women at a GP practice who will be invited to be screened within the next 10 weeks. The purpose of the PNL is to allow GPs to remove women from the list who do not need to be invited for screening (e.g. recent hysterectomy or pregnant). We have requested that NHAIS add women who test HPV positive on a self-sample into the PNL so that they will receive two "reminder" letters to attend for a follow-up (clinician) test.

Self-sampling studies have found that most (~82%) women who test HPV positive attend for follow-up (cytology or colposcopy).(17, 18, 34-36) In our previous study of opportunistically offered SSKs in London, 85% of women who tested HPV positive on a self-sample attended for follow-up investigations.(16) We will collect details of follow up cervical screening tests, colposcopy referrals and histological outcomes for self-sample screen positive women from NHAIS and the central laboratory Cyres colposcopy database (with the women's permission – see section 7.3.2 Consent at individual women level).

As an additional safety-net, when the trial reaches the end of recruitment, all self-sample screen positive women who have not attended for a follow up test will be highlighted to their GP practices who will make one further attempt to contact the women to come for a follow up test. This will be either by telephone call or text message as per GP Practice local procedures. Relevant women will be identified by the participating GP practices (designated trial administrator) using a pre-written search of the GP records or by the laboratory.

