| To estimate the rates of compliance with follow up for women who test HPV positive on a self-sample | *Attendance at follow up (conventional cervical screening test or colposcopy) within 6                                                                                                                                                                                                                                                     | 
Number of women who test HPV positive on a self-sample and
 
(i) have a conventional cervical screening test recorded in NHAIS within 6m of HPV positive
                                                                                                                                                                                                                                                                                                                                                                                                                                                                                                                                                                                                                                                                                                                                                                                                                                                                                                                                                                                                                                                                                                                                                                                                                                                                                                 |

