|                                                                           |                                                                                                                                              |                                                                                                                                                                                                                                                                                                                                                                                                                                                                                                                                                                                                                                   |
|---------------------------------------------------------------------------|----------------------------------------------------------------------------------------------------------------------------------------------|-----------------------------------------------------------------------------------------------------------------------------------------------------------------------------------------------------------------------------------------------------------------------------------------------------------------------------------------------------------------------------------------------------------------------------------------------------------------------------------------------------------------------------------------------------------------------------------------------------------------------------------|
|                                                                           | months of testing HPV positive on a self-sample                                                                                              | (ii) self-sample result as a % of all HPV positive on a self-sample and of these, number who attend colposcopy if conventional cervical screening test is abnormal within 6 months                                                                                                                                                                                                                                                                                                                                                                                                                                                |

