### **7.10 End of Trial**

The end of the active recruitment of the trial will be defined as either when a minimum of 10,000 kits have been returned or at 12 months after study start, whichever is earliest.

The trial will end once a minimum of 6 months of follow-up data (6 months from the last participant recruited) for women testing HPV positive on a self-sample have been received.

The Chief Investigator will inform the REC of the end of the trial within 90 days of its completion. A summary of the final research report will be sent to the REC within 12 months of the end of the trial

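### CIN2+ detection and colposcopy referral ignore unequal follow-up, and the 6-month compliance rate mixes women with and without an in-window GP contact

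*Protocol*

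**What the plan says.** Protocol 3.2 defines compliance as "Attendance at follow up (conventional cervical screening test or colposcopy) within 6" months of a positive self-sample. Measure (i) asks whether women "have a conventional cervical screening test recorded in NHAIS within 6m of HPV positive". Measure (ii) counts the "number who attend colposcopy if conventional cervical screening test is abnormal within 6 months" and gives no start for that limit. Section 9.2.2 repeats the 6-month attendance outcome.

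The same table expresses CIN2+ detection and colposcopy referral each as a percentage of everyone who returns a self-sample. Neither has a follow-up window per woman.

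On reminders, section 7.5.2 says of a woman with a positive self-sample that "her NTDD will be set to 3 months from the date the self-sample was taken". It continues "If a follow up test (conventional cervical screening test) is not received in NHAIS within 10 weeks of the reset NTD (3m" and then places her on her practice's Prior Notification List (PNL), from which two reminder letters follow. It defines the list thus: "The PNL is a list of women at a GP practice who will be invited to be screened within the next 10 weeks". Table 1 (section 7.5.4) has the early recall itself put her on the list and mentions no waiting period.

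The extra GP contact happens once: "when the trial reaches the end of recruitment, all self-sample screen positive women who have not attended for a follow up test" are flagged to their practices for one more attempt. Section 7.10 sets data close: "The trial will end once a minimum of 6 months of follow-up data (6 months from the last participant recruited". Sections 4.3 and 7.8.1.1 give individual follow-up as 6–18 months.

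**The concern.** Two clocks run at once. The compliance endpoint runs from each woman's positive result. The GP contact and data close are calendar dates. How long a woman is observed, and whether the GP contact can count for her, therefore depends on when in recruitment she tested positive.

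For CIN2+ detection and referral, a plain percentage treats a pathway still open at data close as a negative outcome. Raising detection of CIN2+ is one of the two stated aims (section 3.1), so a rate biased low matters.

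For compliance, one figure pools women with and without an in-window GP contact, in proportions set by practice start dates. The pathway is itself under test, so a reader will want to know whether the 6-month figure includes the effect of its reminder letters. As the text stands, that cannot be worked out.

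**Working it through.** **Inputs.** Compliance window 6 months (3.2). Reset due date 3 months after sampling, a 10-week trigger and a 10-week list horizon (7.5.2). GP contact at the end of recruitment (7.5.2). Recruitment 6–12 months per practice, average 9 (9.1.1). Data close 6 months after the last recruit (7.10). One month is 30.44 days, so 3 months is 13.0 weeks and 6 months is 26.1 weeks.

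**1. The plan's own figures.** Follow-up is 6 + 0 = 6 to 6 + 12 = 18 months, as stated. Duration is 12 + 6 + 3 = 21 months, as in the Trial Summary.

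**2. CIN2+ and referral.** A woman positive s months before recruitment ends is followed for 6 + s months. If her outcome would be recorded T months after the positive result, it is missed when T > 6 + s. With even accrual over R months, the share missed among women with that T is (T − 6)/R for T between 6 and 6 + R, and zero for T of 6 or less. The loss therefore needs both a late positive result and a late outcome.

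The protocol does not give T. As an illustration only, assume histology 3 months after the conventional test and attendance as soon as the first reminder arrives:

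- *10 weeks read as after the due date* (letter at 5.3–7.6 months, step 4): T = 8.3–10.6. With R = 12 the share missed is 2.3/12 = 19% to 4.6/12 = 38%. With R = 9 it is 26–51%.
- *10 weeks read as before the due date* (letter by 3.0 months): T is at most 6.0, so nothing is missed.

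These are shares of reminder-prompted women, not of all cases. If 20–40% of eventual cases came through that route (an assumption), the relative loss on the first reading with R = 12 would be 0.20 × 0.19 = 4% to 0.40 × 0.38 = 15%. With R = 9 it would be 0.20 × 0.26 = 5% to 0.40 × 0.51 = 20%. On the second reading it is about nil for prompt responders.

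**3. GP contact.** It falls inside the window only for women positive in the last 6 months of recruitment. With even accrual the share is min(6, R)/R:

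- R = 12: 6/12 = 50%
- R = 9: 6/9 = 67%
- R = 6: 6/6 = 100%

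The share with at least 3 months of window left is 3/R: 25%, 33% and 50%. These are shares of all positive women. Among those still unscreened at the contact the split will differ.

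**4. Reminder letters.**

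- *After the due date:* listing at 13.0 + 10 = 23.0 weeks (5.3 months), first letter in weeks 23–33 (5.3–7.6 months). The window closes at 26.1 weeks from sampling, so (26.1 − 23.0)/10, about 30%, of the letter span lies inside it. If the clock starts at a result 1–3 weeks after sampling (an assumption), this becomes 40–60%.
- *Before the due date:* listing at 13.0 − 10 = 3.0 weeks, first letter by week 13, inside the window.

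The spacing of the second letter is not given.

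**5. Colposcopy limit.** If it starts at the self-sample, a woman whose abnormal test is in month 5 has 6 − 5 = 1 month left. If it starts at the abnormal test, it runs to month 5 + 6 = 11, while the last recruits have 6 months of follow-up.

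**The case against.** A fixed 6-month window is defensible: it is the longest that every participant completes. Every positive woman is advised to attend in her results letter, due within about two weeks of returning the sample (7.4), and the conventional test may be taken at once (7.5.2). The protocol cites attendance of 82–85% in earlier studies, so the reminders and the GP contact act mainly on the remainder. The contact is described as an added safety net, and it leaves 6 months before data close. These are descriptive secondary endpoints in a feasibility trial, and the analysis plan, not shown, may handle timing. All of this stands, and it limits the size of the problem. It does not remove it: section 3.2 itself fixes the endpoints as plain percentages. The models in 9.2.2 adjust for time, but a binary outcome still counts an unfinished pathway as a negative one.

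A reader might infer more than the documents support:

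- *That the letters come too late to count.* This needs the 10 weeks to run after the due date. Table 1 and the forward-looking list definition also fit a first letter by about week 13.
- *That 6-month compliance will fall well below 82–85%.* No time horizon is given for those figures, and no figure for how many women attend only after a reminder.
- *That trial end loses CIN2+ for late attenders generally.* With 6–18 months of follow-up, only women who both test positive late and attend late are affected.
- *That half of positive women cannot have an in-window GP contact.* That is the 12-month case only.

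**Conclusion.** The point holds in three parts of differing strength.

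- **CIN2+ detection and referral** are biased low because follow-up is unequal and unfinished pathways count as no outcome. The direction is clear. The size is unknown and probably modest, since time to histology and the share of late attenders are not given. The percentages in step 2 of the working are illustrations that rest on one reading of the 10-week trigger and on assumed delays.
- **The 6-month compliance rate** pools women who can and cannot have an in-window GP contact. The in-window share is 50%, 67% or 100% for 12, 9 or 6 months of recruitment. This rests only on even accrual.
- **Whether the reminder letters fall inside the window** cannot be determined. This is an inconsistency between section 7.5.2 and Table 1, not a demonstrated timing failure.

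The missing start of the colposcopy limit is a separate gap in the wording of 3.2. Correction is worthwhile because it is cheap and CIN2+ detection is a headline aim.

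**What to change.** 1. Keep the 6-month compliance figure. Add cumulative attendance to 12 months by a time-to-event method from the positive result, and a version censored at the end-of-recruitment GP contact. The censored version has at most 12 months at risk, so it supports the 6-month estimate better than the 12-month one.
2. Estimate CIN2+ detection and colposcopy referral as cumulative incidence at a stated fixed time, with censoring at data close. The later part of the curve will rest on women and practices recruited early, and the report should say so.
3. State in 3.2 when the 6-month colposcopy limit starts. Report time from abnormal test to colposcopy with censoring at data close, because a full 6 months after the abnormal test will not be observable for late recruits.
4. Reconcile section 7.5.2 with Table 1 on the timing of PNL entry, so that the window can be read against the letters. No view is taken here on which rule is right.

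The cost is endpoint wording and some added analysis. The dated test, colposcopy and histology records are already to be collected (10.4.1, 10.4.3). A later Cyres extract would capture more outcomes, but it would be an addition. The 13-month extract in 10.4.1 is aggregate NHAIS coverage data that is only optional, and the 3- and 6-year CIN2+ follow-up depends on future funding (7.8.1.2).
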